### Data management

According to the §13 of the German Good Clinical Practice (GCP) Regulation, all important trial documents (e.g., CRF) will be archived for at least 10 years after the trial termination. According to the §28c of the German X-Ray Regulation and the §87 of the German Radiation Protection Regulation, the informed consent forms including patients’ consent for trial participation, application of irradiation, and data transmission to the competent authority will be archived for at least 30 years after the trial termination. The study center at the Department of Radiation Oncology will be responsible for archiving the trial master file (TMF) including protocol, CRF, report, and so on. The investigator(s) will archive all trial data [data and Investigator Site File (ISF)] including subject identification list and relevant correspondence) according to the section 4.9 of the International Council for Harmonisation of Technical Requirements for Registration of Pharmaceuticals for Human Use (ICH) Consolidated Guideline on GCP (E6) and to local law or regulations. The Subject Identification List will be archived for at least 15 years after the trial termination. If an investigator relocates, retires, or for any reason withdraws from the study, the principal investigator should be notified prospectively. The study records must be transferred to an acceptable designee, such as another investigator or another institution.

### Study design

The trial is designed as a single-center, dose escalation study. Patients fulfilling the inclusion and exclusion criteria will be allocated to neoadjuvant SRS and assigned to four different cohorts depending on tumor size. Within each cohort, there are 3 different dose levels. The treatment contains neoadjuvant SRS according to the protocol, tumor resection according to imaging findings, and postoperative neuropathological evaluation.

### Objectives

The primary objective is to determine the maximum tolerated dose (MTD). Secondary objectives are to evaluate further parameters such as survival and tumor characteristics, assessment of QoL, clinical neurological and neurocognitive functions.

### Endpoints

The primary endpoint is the MTD for which no dose-limiting toxicities (DLTs) occur. DLTs will be evaluated according to the Common Terminology Criteria for Adverse Events (CTCAE) version 5.0 (2017) continuously during the study until the first follow-up visit (4–6 weeks after surgery) for each patient and each dose level. Central nerve system necrosis (≥ grade 3), cerebrospinal fluid leakage (≥ grade 4), wound infection ((≥ grade 4), wound dehiscence (≥ grade 4), postoperative hemorrhage (≥ grade 4), cognitive disturbance (≥ grade 4), cerebral edema (≥ grade 4), headache (≥ grade 4), and seizure (≥ grade 4) are defined as DLTs.

Secondary endpoints are as follows:Central nerve system necrosis of CTCAE grade 1–3.Cerebrospinal fluid leakage of CTCAE grade 1–3.Wound infection of CTCAE grade 1–3.Wound dehiscence of CTCAE grade 1–3.Cerebral edema of CTCAE grade 1–3.Local control rates.OS and progression-free survival (PFS) at 12-month follow-up.Time interval between treatment initiation of neoadjuvant SRS and start of systemic chemotherapy.Health-related QoL evaluated using the EuroQoL questionnaire.Neurocognitive function assessed using the Minimal Mental State Examination (MMSE) test.Late toxicity of CTCAE grade 1–5.Immunological and molecular parameters [such as programmed death-ligand 1 (PD-L1) expression, Rapidly Accelerated Fibrosarcoma type B (BRAF) gene mutation, epidermal growth factor receptor (EGRF) mutation, and anaplastic lymphoma kinase [ALK] translocation on the resected specimen].

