### Statistical analyses

The traditional “3 + 3” design remains the prevailing method for conducting phase I cancer clinical trials [32, 33]. It requires no modelling of the dose-toxicity curve beyond the classical assumption for cytotoxic drugs that toxicity increases with dose. This rule-based design proceeds with cohorts of 3 patients. The first 3 patients in the first cohort will be treated at a starting dose that is considered to be safe based on extrapolation. If none experiences a TLD at that dose level, the following 3 patients will be treated at the next higher dose level. The MTD for which no DLT occur will be evaluated according to the CTCAE Version 5.0 (2017) continuously during the study until first follow up (4–6 weeks after surgery) for each cohort and dose level. A DLT is defined as central nerve system necrosis (≥ grade 3) or cerebrospinal fluid leakage (≥ grade 4) or wound infection (≥ grade 4) or wound dehiscence (≥ grade 4) or postoperative hemorrhage (≥ grade 4) or cognitive disturbance (≥ grade 4) or cerebral edema (≥ grade 4) or headache (≥ grade 4) or seizure (≥ grade 4). If no DLT occurs in one dose level, another 3 patients will be treated at the next higher dose level. However, if any of the first 3 patients experiences a DLT, the following 3 patients will be treated at the same dose level. At the highest dose level, at least 6 patients will be treated. Thus, the maximum number of patients enrolled in this study will be 4 × 6 × 3 = 72. Dose will be prescribed to the 80% isodose for linear accelerator (LINAC)-based radiotherapy. The dose escalation continues until at least 2 patients in a cohort of 3–6 patients experience DLTs (i.e., 33% of patients with DLTs at that dose level). The recommended dose for a future phase II trials is conventionally defined as the dose level just below the toxic dose level.

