The primary endpoint of this study is safety assessed from the start of radiotherapy until the first follow up after surgery (4–6 weeks after surgery). Based on experience from clinical practice, the number of patients lost to follow-up is expected to be very small. Patients who dropped out of the study between radiation treatment and first follow-up visit will be replaced by a new patient. For patients without a final examination after 1 year, the last valid examination will be used for the assessment of secondary endpoints. All secondary endpoints will be analyzed in an explorative manner using appropriate statistical methods: Mann–Whitney *U* Test (acute toxicity of CTCAE grade 1–3; late toxicity of CTCAE grade 1–5, immunological parameters, time interval between treatment initiation and start of systemic chemotherapy), Fisher’s exact test or Chi-square test (local control rates), log-rank test and Kaplan–Meier curves (OS and PFS at 12-month follow-up), Student *t* test (neurocognitive function), and scaled *t* test (health-related QoL) for independent patients.

The following parameters will be collected and taken into account in analyses applying regression models: age, Karnofsky performance score, extent of neurosurgical resection, recursive partitioning analysis (RPA)-classification.

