### Assessment of endpoints

The primary endpoint, MTD, will be assessed through extensive anamnesis and clinical neurological examination on the first postoperative day, the day of discharge from hospital, and the first follow-up visit at 4–6 weeks after surgery, with wound healing evaluated by an experienced neurosurgeon. This study will use the CTCAE version 5.0 for toxicity and adverse event reporting. Postoperative MRI (1–2 days after surgery) and the first follow-up MRI (4–6 weeks after surgery) will be evaluated by an experienced neuroradiologist, and the efficacy will be assessed according to the RECIST criteria [34].

For secondary endpoints, anamnesis and clinical neurological examination will be conducted as mentioned above. Disease progression is defined as radiological or neurological/clinical progression (whichever occurs first); PFS is considered the time interval between the date of treatment initiation and the date of disease progression or death, whichever occurs first. If neither event is observed, the patient will be censored at the date of the last follow-up examination. Neurocognitive function, QoL, and late toxicities will be evaluated at each follow-up visit every 3 months or at neurological deterioration (Table 2). Neuropathological work-up on the resected specimen will follow standard operating procedures at the Department of Pathology and will include immunologic as well as molecular parameters, such as PD-L1 expression, BRAF-gene mutation, EGFR mutation, and ALK translocation, where appropriate. Follow-up assessments (including MRI or CT) will be performed as described until disease progression (even after the termination of the study) in accordance with GCP and the treatment guidelines for patients with intracerebral metastases.

**Table 2 Tab2:** Time schedule of this study

Timepoint	Enrollment	Treatment				Follow-up (months)				Close-out (months)
	Day 0	Preoperative RT Day 1	Resection Days 2–7	Postoperative Days 1–2	Postoperative Days 3–5	1,5	3	6	9	12
Enrollment										
Eligibility screening	X									
Informed consent	X									
Study visit	X	X			X	X	X	X	X	X
Planning CT	Within 1–7 days after enrollment									
Planning MRI	Within 1–7 days after enrollment									
Interventions										
Neoadjuvant SRS		X								
Resection			X							
Assessments										
MRI	X			X		X	X	X	X	X
Clinical-neurological examination	X	X	X	X	X	X	X	X	X	X
Minimental state examination	X					X	X	X	X	X
Health-related QoL	X				X	X	X	X	X	X

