
Vetlova et al. [23] analyzed a cohort of 19 patients with 22 metastases who underwent neoadjuvant SRS. The median tumor volume was 14.1 mL (range 3.0–57.1 mL), and the applied dose was 18 Gy in median (range 12.6–24.4 Gy), the surgery was carried out within 24–48 h after SRS. Two patients had local recurrence after 5.5 and 17.4 months of follow-up, and 1 had radiation necrosis at 4.6 months after treatment. Two patients died of disease progression.

The concept of neoadjuvant SRS for intracerebral metastases is characterized by a number of potential benefits compared with postoperative radiosurgery. Mostly, RT of the intact intracerebral metastases and surrounding normal tissues leads to a better definition of the target volume for RT, because postoperative changes, such as ischemia, scar tissue or blood-remnants, are missing. Therefore it is easier to spare normal tissue and consequently it can result in a higher safety of effective treatment of all tumor cells and subsequent lower damage to surrounding normal tissues. Additionally, the surgical tract does not exist before surgery; therefore, this area can be spared completely. Thereby, the rate of postoperative complications such as wound healing disorders and cerebrospinal fluid leaks could be reduced. After preoperative RT systemic chemotherapy or targeted therapy can be rapidly initiated after wound healing if needed in case of a high extracranial tumor burden. Contrary, systemic therapy is often delayed until postoperative RT is finished since some cancer therapies may not be applied during RT of the central nervous system or with high single doses.

This phase I study aims to find an optimal dose for neoadjuvant SRS for safe surgery and hence good outcome and local control. The trial incorporates a margin accounting for the microscopic spread and focuses on the dose escalation of this treatment strategy as well as QoL and neurocognitive function.

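### The DLT window closes at each patient's first follow-up visit, 28 to 42 days after surgery, so the same event in weeks 4–6 can be a DLT in one patient and not in another

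*Protocol article*

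**What the plan says.** The protocol article ties the end of DLT evaluation to a visit wherever it mentions it.

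- Endpoints: DLTs are evaluated "continuously during the study until the first follow-up visit (4–6 weeks after surgery) for each patient and each dose level".
- Statistical analyses: the MTD is evaluated "continuously during the study until first follow up (4–6 weeks after surgery) for each cohort and dose level". The same section describes the primary endpoint as "safety assessed from the start of radiotherapy until the first follow up after surgery (4–6 weeks after surgery".
- Assessment of endpoints: the last assessment of the primary endpoint is "the first follow-up visit at 4–6 weeks after surgery, with wound healing evaluated by an experienced neurosurgeon".
- The Methods part of the Abstract gives the same end for adverse events.

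No last day is named. Toxicity after the visit is still recorded, but as adverse events or as late toxicity, which is a secondary endpoint.

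Under Statistical analyses, any DLT among the first 3 patients adds 3 more at the same level. Escalation ends once 2 or more of the 3 to 6 patients have had a DLT.

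Table 2 heads its first follow-up column 1,5 months ("Postoperative Days 3–5 1,5 3 6 9 12") and gives no time origin for it.

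**The concern.** A visit range of two weeks is ordinary for descriptive safety data. Here the visit also closes the window for the one count on which every dose decision depends. Two patients treated exactly as planned can be observed for different lengths of time. The same grade 4 wound dehiscence, wound infection, cerebral edema or seizure on day 35 after surgery is then a DLT in the patient whose visit falls on day 42, and is not one in the patient already seen on day 28.

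With so few patients per level, one event more or less can decide whether a level is expanded, whether escalation goes on, and which dose is named as the MTD. DLT counts from different levels and size cohorts may also rest on unequal observation.

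**Working it through.** **The plan's own figures.** The article gives no error rate or power for the 3+3 rule. Its sample sizes reproduce: 4 × [(3 × 3) + 3] = 48 and 4 × 6 × 3 = 72. The point below does not affect them.

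**Length of the window.**
- After surgery: 4 × 7 = 28 days to 6 × 7 = 42 days. The spread is 14 days and the ratio 42/28 = 1.5.
- From radiosurgery on Day 1, with the operation 1 to 6 days later (Table 2: "Resection Days 2–7"): 1 + 28 = 29 days to 6 + 42 = 48 days.

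**Table 2 label.** 1.5 × 30.44 = 45.7 days, or 6.5 weeks. Counted from surgery, that is 3.7 days past week 6. Counted from Day 0 with resection on Days 2–7, it is 45.7 − 7 = 38.7 to 45.7 − 2 = 43.7 days after surgery, or 5.5 to 6.2 weeks.

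**Effect on the 3+3 decision.** Let p be the chance that a patient has a counted DLT. A level is not called toxic if 0 of 3 patients have one, or if 1 of the first 3 and 0 of the next 3 do:

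P(toxic) = 1 − (1−p)³ − 3p(1−p)²(1−p)³

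Full observation to day 42:
- p = 0.20: 1 − 0.512 − 0.197 = 0.291
- p = 0.30: 1 − 0.343 − 0.151 = 0.506

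The article does not say when DLTs arise or how visits are distributed. Three assumed cases show the range. P42 is the true 6-week risk.

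- **A. A tenth of DLTs fall in weeks 4–6; visits and these events are spread evenly over those weeks.** Half of that tenth is missed, so p = 0.95 × P42 = 0.190 (0.285).
- **B. Constant hazard, visits spread evenly.** h = −ln(1−P42)/42 = 0.00531 (0.00849) per day. The mean counted risk over days 28 to 42 is p = 1 − [exp(−28h) − exp(−42h)]/(14h). This gives 1 − (0.8618 − 0.8)/0.0744 = 0.1695, and 1 − (0.7884 − 0.7)/0.1189 = 0.2567.
- **C. Constant hazard, every visit at day 28.** p = 1 − (1−P42)^(28/42) = 0.138 (0.212).

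| Case | p at P42 = 20% | P(toxic) | p at P42 = 30% | P(toxic) |
|---|---|---|---|---|
| All observed to day 42 | 0.200 | 0.291 | 0.300 | 0.506 |
| A | 0.190 | 0.270 | 0.285 | 0.475 |
| B | 0.1695 | 0.226 | 0.2567 | 0.415 |
| C | 0.138 | 0.163 | 0.212 | 0.317 |

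If a tenth of DLTs fall in weeks 4–6 but every visit is at week 4, then p = 0.18 (0.27) and P(toxic) = 0.248 (0.443), which lies between A and C.

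**The case against.** **The event is not lost.** Adverse events are recorded again at 3, 6, 9 and 12 months. An independent board reviews them at least twice a year and may recommend changing or ending the trial (Monitoring). This is true, and it is a real safeguard for patients. It does not bring the event back into the DLT count, which alone drives the dose decisions.

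**The article condenses a fuller protocol, which may hold visit-window rules.** That would answer a complaint about a missing detail. This is a stated rule for the primary endpoint, given in the same form in several sections. A different cut-off elsewhere would depart from it.

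**Most of these events come early.** Postoperative hemorrhage, cerebrospinal fluid leakage and the wound complications are tied to the operation, so a constant hazard probably puts too many DLTs in weeks 4–6. This stands, and it is why the effect is given as a range.

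**Two stronger readings do not hold.** A reader might take the 1,5-month column to contradict the text. Table 2 states no origin, and its axis begins at enrolment. From there the column falls almost wholly within the text's range, and it may simply be a nominal label for about six weeks. It is loose, not contradictory.

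A reader might also infer that fast-healing patients, or those needing systemic therapy, would be seen early. The Discussion says only that "After preoperative RT systemic chemotherapy or targeted therapy can be rapidly initiated after wound healing if needed". It says nothing about when the study visit is booked, and nothing shows that visit timing would differ between levels or cohorts.

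**Conclusion.** The point holds in a limited form. The stated rule allows observation after surgery to differ by up to 14 days between patients, and it classes identical events in weeks 4–6 differently. This follows from the text and needs no assumption.

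The size does need assumptions. For a 6-week DLT risk of 20%, the chance of calling a level toxic falls from 29% to between about 27% and 16%. For a risk of 30% it falls from 51% to between about 47% and 32%. The lower ends join a constant hazard to every visit at week 4. They mark the extreme and should not be read as the expected loss, particularly as Table 2 places its nominal visit near week 6. The documents do not support a claim of systematic bias between levels. What they show is a primary-endpoint window that partly depends on the appointment date. The 48 to 72 patients planned are unaffected.

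**What to change.** End the DLT window on one fixed day after surgery for every patient, whatever the date of the visit. Change it wherever the window is given: the Methods part of the Abstract, Endpoints, both places in Statistical analyses, and Assessment of endpoints. Day 42, the upper limit the plan already allows, is the natural choice; the trial team should confirm the final day. The rule that replaces patients who drop out before the first follow-up visit should refer to the same day.

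For patients seen earlier, confirm DLT status up to that day by telephone or from the chart. Take the escalation decision once all patients at the level have passed it. In Table 2, state the time origin of the 1,5-month column and align its label with the 4–6 week visit.

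The cost is a call or chart check for patients seen early and a wait of up to two weeks longer per level. A telephone check is also less sensitive than the examination and MRI at the visit, so the fix equalises the length of observation more fully than its depth.

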### Data collection, management, and analysis

As used in this study, the term Case Report Form (CRF) should be understood to refer to a paper form or an electronic data record or both, depending on the data collection method used in this trial. For this trial, relevant data will be documented in paper-printed CRFs. All findings including clinical and laboratory data will be documented in the subject’s medical record and in the CRF by the investigator or an authorized member of the study team. The investigator is responsible for ensuring that all sections of the CRF are completed correctly and that entries can be verified against source data. In some cases, the CRF, or part of the CRF, may also serve as source documents: Karnofsky Performance Status, Documentation of Clinical-Neurological Examination. In these cases, a document should be available at the investigator’s site and clearly identify those data that will be recorded in the CRF, and for which the CRF will stand as the source document. There is no financial compensation for the participant. In case that the participant discontinues the study, documented medical parameters will not be collected and used for statistical analysis. In case of deviation from intervention protocol, e.g., no SRS prior to resection, the participant is excluded from the study.

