### Neurosurgery

For optimal surgical planning, all patients will have an MRI for navigation purposes. For eloquent lesions (less than 2 cm distance between the metastases and the corticospinal tract or the Broca’s area), intraoperative neuromonitoring utilizing direct cortical and subcortical electrical stimulation and navigated transcranial magnetic stimulation will be performed to minimize the risk of new neurological deficit [28–31]. Tumor resection will be carried out according to microsurgical standards. Surgical parameters, such as estimated blood loss, duration of surgery, need for blood transfusions, and complications will be documented in a standardized fashion. To reflect the daily practice and not the best surgical approach for individual cases, there will be no mandate on a specific surgical approach, and each center will decide the surgical approach independently. For the same reasons, individual surgical experience cannot be taken into consideration, but experienced centers have been selected. Postoperative MRI for resection control will be done in all patients, thereby special emphases will also be drawn for postoperative ischemia. Postoperative care is not standardized in the study protocol. The use of analgesics and cortisol follows the local routine, but needs to be documented.

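### The closed list of nine DLT terms alone drives escalation, so a treatment-related death in the DLT window under any other term does not count against the dose level

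*Protocol article*

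**What the plan says.** **DLT definition.** The Endpoints section lists central nervous system necrosis from grade 3, and from grade 4 cerebrospinal fluid leakage, wound infection, wound dehiscence, postoperative hemorrhage, cognitive disturbance, cerebral edema, headache and finally "seizure (≥ grade 4) are defined as DLTs". Statistical analyses gives the same nine terms joined by *or*: "A DLT is defined as central nerve system necrosis (≥ grade 3) or cerebrospinal fluid leakage (≥ grade 4) or wound infection (≥ grade 4", and so on. Neither list has a clause for death or for other grade 4 or 5 events.

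**Window.** The primary endpoint is described as "safety assessed from the start of radiotherapy until the first follow up after surgery (4–6 weeks after surgery").

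**Escalation.** Under Statistical analyses, a level with no DLT leads to the next level. Any DLT among the first three adds three patients at the same level. Escalation ends once at least 2 of 3 to 6 patients have a DLT.

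**Patients who leave.** Statistical analyses states: "Patients who dropped out of the study between radiation treatment and first follow-up visit will be replaced by a new patient". Data collection, management, and analysis adds: "In case that the participant discontinues the study, documented medical parameters will not be collected and used for statistical analysis". Neither section says whether a patient who dies falls under it.

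**Related text.** The Neurosurgery section says of the postoperative MRI that "special emphases will also be drawn for postoperative ischemia". Ischemia is neither a DLT nor a named secondary endpoint. The Monitoring section has an independent board review adverse events at least twice a year and make recommendations.

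**The concern.** In a 3+3 design the DLT count is the only information that moves the dose. If a death caused by the study treatment falls outside the count, the rule treats that patient as having tolerated the dose. Any resulting error is in one direction, toward higher levels and a higher recommended phase II dose.

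The gap follows from a definition stated twice in full. It is not a detail the article passes over. If such a death occurred, the team would have to choose between applying the written rule, and so escalating, and changing the DLT definition with the outcome already known. Neither is satisfactory for a primary endpoint.

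**Working it through.** **Step 1. The plan's own figures.** Minimum 4 × [(3 × 3) + 3] = 48; maximum 4 × 6 × 3 = 72. Both reproduce. They depend on level sizes, not on what counts as a DLT.

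**Step 2. Which deaths count.** All nine thresholds are open upward, so a grade 5 event under any listed term is a DLT. A grade 5 event under any other term is not.

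**Step 3. What the rule then does.**

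| Events at a level | Count as written | Action as written | Count if the death were a DLT | Action if it were |
|---|---|---|---|---|
| One unlisted treatment-related death among the first 3, no listed DLT | 0/3 | escalate | 1/3 | add 3 at the same level |
| One listed DLT and one unlisted treatment-related death among 6 | 1/6 | escalate | 2/6 | stop |

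In both rows the deceased patient stays in the denominator, so replacement plays no part.

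**Step 4. Size.** The document gives no rates. Assume a listed-DLT probability of 0.10 per patient and an independent probability q of an unlisted treatment-related death in the window, with q = 0.01, 0.02 or 0.03.

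For a level entered with three patients (levels I and II), the rule escalates on 0/3, or on 1/3 followed by 0/3:

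P(toxic) = 1 − [(1 − p)³ + 3p(1 − p)²(1 − p)³]

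As written, p = 0.10: 1 − (0.7290 + 0.1771) = 0.094, whatever the value of q.

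If these deaths count, p = 1 − 0.9(1 − q):

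| q | p | (1 − p)³ | 3p(1 − p)⁵ | P(toxic) | Difference from as written |
|---|---|---|---|---|---|
| 0.01 | 0.109 | 0.7073 | 0.1836 | 0.109 | 1.5 points |
| 0.02 | 0.118 | 0.6861 | 0.1889 | 0.125 | 3.1 points |
| 0.03 | 0.127 | 0.6653 | 0.1932 | 0.141 | 4.8 points |

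Differences are from unrounded values (for example 0.1415 − 0.0939 = 0.0476).

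**Step 5. How often the first row of Step 3 would arise.** The chance that the first three patients at a level have no listed DLT but at least one such death is 0.729 × [1 − (1 − q)³] = 2.2%, 4.3% or 6.4% for q = 0.01, 0.02 or 0.03.

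**Step 6. Across the whole trial.** The chance of at least one such death is 1 − (1 − q)^48 = 38%, 62% or 77% with 48 patients, and 1 − (1 − q)^72 = 52%, 77% or 89% with 72. This is the chance that the situation occurs at all, not the chance of a wrong dose decision.

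**Step 7. Replacement.** The replacement sentence neither defines drop-out nor excepts death. If a deceased patient were treated as a drop-out, that patient would also leave the denominator. This is a separate ambiguity, and Steps 2 to 6 do not use it.

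**The case against.** The strongest defence is that a radiation dose-finding trial may reasonably limit its DLTs to events plausibly driven by the radiation. The list already covers fatal necrosis, hemorrhage, edema, seizure, wound problems and cerebrospinal fluid leakage. What remains may come mainly from surgery or from the systemic cancer. Ischemia appears only in the postoperative imaging text, and nothing there links it to radiosurgery dose. This stands against counting every death. It does not answer the case of a death judged related to the study treatment, which the list also excludes.

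Second, such a death would not go unseen: adverse events are assessed continuously, and the independent board may recommend modification or termination. That is true, but the board's review is advisory, is promised at least twice a year, and is not tied to dose-level decisions.

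Third, the full protocol is not shown and might add a clause. It might, but the article gives the definition twice as complete.

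Two stronger readings are not supported. A reader might infer that the plan replaces patients who die and so removes them from the count. No section calls a death a drop-out; the replacement sentence follows one on loss to follow-up, and death is handled elsewhere as a survival event. Replacement of a deceased patient is a permitted reading, not a stated rule. A reader might also infer that the list contradicts the statement that "The primary endpoint of this study is safety assessed from the start of radiotherapy until the first follow up after surgery". A safety window combined with a defined list of dose-limiting events is not a contradiction.

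**Conclusion.** The point holds in this limited form: as written, a treatment-related death in the window under a term outside the nine is not a DLT, and a level with such a death can escalate at 0/3 or 1/6. This follows from the definition and the escalation rule alone. The undefined drop-out wording is a secondary ambiguity that could make matters worse.

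The effect on a single decision is modest: about 1.5 to 4.8 percentage points in the chance of declaring a level toxic. That range rests on an assumed 10% listed-DLT rate, assumed unlisted-death rates of 1% to 3%, and independence, so it is illustrative. The case for a change rests less on that average than on what the rule does when such a death occurs. The change should be made; it does not call the 3+3 structure or the sample size into question.

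**What to change.** Reconcile four places: the DLT definition under Endpoints, its repeat under Statistical analyses, the replacement sentence under Statistical analyses, and the sentence on discontinued participants under Data collection, management, and analysis. They should together state that:

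1. A treatment-related death between the start of radiosurgery and the first follow-up visit enters the DLT count whatever its CTCAE term. The wording on attribution to radiosurgery or resection is for the investigators to set.
2. Replacement covers only patients who leave alive and without a DLT, and the rule on discontinued participants' data does not remove a death or a DLT from the count.

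The cost is about two sentences, with 48 and 72 unchanged. The downside is that a death due mainly to surgery may occasionally count against a dose level, which errs toward caution.

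### The time-to-systemic-therapy endpoint stops only at chemotherapy and is assigned to a Mann–Whitney test that gives no value to patients who die first or never start

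*Protocol article*

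**What the plan says.** In the Protocol article, the Endpoints section lists among the secondary endpoints the "Time interval between treatment initiation of neoadjuvant SRS and start of systemic chemotherapy". The Statistical analyses section places the "time interval between treatment initiation and start of systemic chemotherapy" in the list of variables for the Mann–Whitney U test. Methods that handle censoring are named for other endpoints only: "log-rank test and Kaplan–Meier curves (OS and PFS at 12-month follow-up").

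The one censoring rule stands in the PFS definition under Assessment of endpoints: "If neither event is observed, the patient will be censored at the date of the last follow-up examination". Two general rules could also touch this endpoint. For patients without the one-year examination, "the last valid examination will be used for the assessment of secondary endpoints" (Statistical analyses). For participants who discontinue, "documented medical parameters will not be collected and used for statistical analysis" (Data collection, management, and analysis).

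The rationale is not worded uniformly. The Abstract background speaks first of a possible delay to systemic therapy and then of an earlier start of systemic chemotherapy; the Abstract discussion names chemotherapy. The main Discussion is wider: "After preoperative RT systemic chemotherapy or targeted therapy can be rapidly initiated after wound healing", with the condition that it is needed because of extracranial disease.

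**The concern.** Two features that the document states, rather than leaves open, do not fit the purpose of the endpoint.

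The first is the event. Only chemotherapy stops the clock, yet the benefit described includes targeted therapy. The Background says that two thirds of these metastases come from lung cancer, breast cancer and melanoma and stresses new systemic agents. The Endpoints section itself collects PD-L1, BRAF, EGFR and ALK. Some patients can therefore be expected to receive something other than chemotherapy as their next systemic treatment, and the literal definition does not count that start.

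The second is the method. A Mann–Whitney test needs a value or rank for each patient. A patient who dies first, or never becomes fit to start, has no interval. That absence may carry information: a serious wound, cerebrospinal fluid or neurological complication can be the very reason for not starting. If only starters are summarised, a dose level at which fewer patients reach systemic therapy can look the same as one at which nearly all do.

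**Working it through.** **1. Event against rationale.** The endpoint names chemotherapy. The Abstract background uses both the general and the narrow term for the same idea. The Discussion adds targeted therapy. The texts can be reconciled only if chemotherapy is loose wording for systemic therapy, and the article does not say so. Under the literal reading a targeted start is not an event; under the loose reading it is. The same patient can thus be recorded in two ways.

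**2. Method against data type.** This interval is listed under Mann–Whitney, OS and PFS under Kaplan–Meier and log-rank. The censoring rule belongs to PFS. The last-valid-examination rule cannot supply the date of a start that never happened. The discontinuation rule removes data instead of censoring them. No rule in the article gives a non-starter a value or a rank.

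**3. The plan's own figures.** Minimum 4 × [(3 × 3) + 3] = 48 and maximum 4 × 6 × 3 = 72; both reproduce. No figure, effect size or comparison group is stated for this endpoint.

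**4. Illustration: patients with a value.** Let q be the share who never start (assumed, 10% to 50%; the documents give none). Patients with a value = N(1 − q).
- N = 48: 48 × 0.9 = 43.2 down to 48 × 0.5 = 24.
- N = 72: 72 × 0.9 = 64.8 down to 72 × 0.5 = 36.

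**5. Illustration: the median.** Assume that starters begin after a 4-week lag plus an exponential time with median 2 weeks, so their median is 6 weeks whatever q is. Counting never-starters as not started, the all-patient median is 4 − ln(1 − 0.5/(1 − q)) / (ln 2 / 2).

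| q | Starters only (weeks) | All patients (weeks) |
|---|---|---|
| 10% | 6.0 | 6.3 |
| 20% | 6.0 | 6.8 |
| 30% | 6.0 | 7.6 |
| 40% | 6.0 | 9.2 |
| 50% | 6.0 | not reached |

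**6. Illustration: two groups.** Let groups A and B have the same timing among starters but never-start shares qA and qB, with p = 1 − q. Among starters only, the Mann–Whitney probability that an A patient starts before a B patient is 0.50. With never-starters ranked last and ties counted as one half, it is 0.5·pA·pB + pA·qB + 0.5·qA·qB.
- 10% against 30%: 0.5 × 0.9 × 0.7 + 0.9 × 0.3 + 0.5 × 0.1 × 0.3 = 0.315 + 0.27 + 0.015 = 0.60.
- 10% against 50%: 0.5 × 0.9 × 0.5 + 0.9 × 0.5 + 0.5 × 0.1 × 0.5 = 0.225 + 0.45 + 0.025 = 0.70.

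The whole difference lies in the share who start, and the starters-only analysis shows none of it.

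**The case against.** The strongest reply is that this is one exploratory secondary endpoint in a phase I dose-finding trial, reported in an article. Handling of non-starters is commonly left to an analysis plan, and Mann–Whitney is rank-based, so non-starters could be ranked last. The article nowhere says that they are excluded. Much of this stands: a reader might infer that a starters-only analysis is fixed, and the text does not support that. What remains is that the article names a test that does not itself handle censoring or death before start, and gives the censoring methods to OS and PFS alone.

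Chemotherapy may also be shorthand, since both Abstract statements of the benefit use that word. This makes the first feature an ambiguity, not proof that targeted starts would go uncounted. It still needs one clarifying phrase before data are recorded on the paper CRFs. Some non-starters, moreover, will have had no need of systemic treatment and are not delayed patients. That is right, and it is why they should be reported separately.

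A reader might further infer that starting the clock at SRS hides 1 to 7 days of delay. The documents do not support this. The Table 2 entry "Within 1–7 days after enrollment" is a window for the planning scans, and the same table puts preoperative radiotherapy at Day 1. An origin at SRS covers radiosurgery, surgery and wound healing, and matches the PFS origin. It leaves out the time from diagnosis, up to 3 weeks under Patient selection, but an origin at enrollment would also leave out the wait before enrollment.

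**Conclusion.** The point holds as a limited, cheaply corrected flaw. The event is narrower than the rationale, and the named test leaves patients who die first or never start without a value unless a rule is added. How much this matters depends on two shares that the documents do not give: patients whose next systemic treatment is not chemotherapy, and patients who never start. The figures above are illustrations on assumed inputs; they show the mechanism and do not predict the trial's result. Any statement that the endpoint covers a particular fraction of patients would rest on assumption alone.

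A reader might also conclude that the definition is what prevents the trial from testing its claim of earlier systemic treatment. That goes too far. Every patient is allocated to neoadjuvant SRS (Study design), so an earlier start than with postoperative radiotherapy cannot be shown under any definition. The article words the benefit as a possibility and does not list it under Objectives. The primary endpoint, the DLT rules and the sample size of 48 to 72 are not affected.

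**What to change.** - In Endpoints, define the event as the start or restart of any systemic anticancer therapy: chemotherapy, targeted therapy, immunotherapy or endocrine therapy.
- Keep the origin at the start of neoadjuvant SRS. Time from resection can be added as a second figure.
- In Statistical analyses, replace the Mann–Whitney test for this endpoint with cumulative incidence, treating death before start as a competing event and censoring at last follow-up. For participants who discontinue, state how this fits with the rule on not using their data.
- Report separately patients for whom no systemic therapy was planned and those whose therapy continued without a break.
- Present the result descriptively, and say that without a postoperative-radiotherapy arm it cannot show an earlier start.

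The cost is a few CRF items (date and class of the first systemic therapy, and whether therapy was planned or ongoing) and a slightly more involved analysis. The reported figure may be less favourable than one from starters alone.
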